## **7.2 Volunteer Exclusion Criteria:**

1. Confirmed HIV-1 or HIV-2 infection; confirmed HCV, HBV, or syphilis infection
2. Current or planned participation in another clinical trial of an experimental agent during the study period
3. Pregnant or lactating
4. Significant acute or chronic disease, including inflammatory bowel disease or other chronic gastrointestinal disease, immunodeficiency syndrome, or condition requiring immunosuppressant medications (the use of topical or inhaled steroids is permitted)
5. Use of anticancer, antituberculosis or other medications considered significant by the investigator within the previous 6 months
6. Receipt of live-attenuated vaccine within the previous 60 days or planned receipt within 60 days after vaccination with Investigational Product (within 14 days for live attenuated influenza vaccine [LAIV]); or receipt of other vaccine (e.g., influenza, pneumococcal), allergy treatment with antigen injections or tuberculin

- skin test within the previous 14 days or planned receipt within 14 days after vaccination with Investigational Product
7. Receipt of blood transfusion or blood-derived products within the previous 3 months
  8. Receipt of HIV vaccine(s) in a prior HIV vaccine trial. For volunteers who have received control/placebo in an HIV vaccine trial, the Medical Monitor will determine eligibility on a case-by-case basis.
  9. Previous severe local or systemic reactions to vaccination
  10. History of splenectomy
  11. History of seizure in the last 3 years (volunteers with a history of seizures who have neither required medications nor had a seizure for 3 years are not excluded)
  12. Known autoimmune disease
  13. Asthma other than mild, well-controlled asthma. Exclude a volunteer who:
    - Generally uses a bronchodilator (beta 2 agonist) weekly, or
    - In the past year has (any of the following):
      - Had > 1 exacerbation of symptoms treated with oral steroids
      - Routinely used moderate to high dose inhaled corticosteroids (e.g., more than the equivalent of 250 mcg fluticasone; 400 mcg budesonide; 500 mcg beclomethasone; or 1000 mcg triamcinolone/flunisolide, as a daily dose) or theophylline
      - Needed emergency care, urgent care, hospitalization, or intubation for asthma
    - Prophylactic bronchodilator use prior to exercise is not exclusionary
  14. Diabetes mellitus type 1 or type 2, including cases controlled with diet alone. (Not excluded: history of isolated gestational diabetes.)
  15. Thyroidectomy, or thyroid disease requiring medication during the last 12 months
  16. Angioedema within the last 3 years if episodes are considered serious or have required medication within the last 2 years
  17. Hypertension:
    - If a person has been diagnosed with hypertension during screening or previously, exclude for hypertension that is not well controlled. Well-controlled hypertension is defined as blood pressure consistently  $\leq 140$  mm Hg systolic and  $\leq 90$  mm Hg diastolic, with or without medication, with only isolated, brief instances of higher readings, which must be  $\leq 150$  mm
    - If a person has NOT been diagnosed with hypertension during screening or previously, exclude for systolic blood pressure  $\geq 150$  mm Hg at enrollment or diastolic blood pressure  $\geq 90$  mm Hg at enrollment

18. Body mass index (BMI)  $\geq 40$ ; or BMI  $\geq 35$  with 2 or more of the following: systolic blood pressure  $> 140$  mm Hg, diastolic blood pressure  $> 90$  mm Hg, current smoker, known hyperlipidemia
19. Bleeding disorder diagnosed by a doctor (e.g. factor deficiency, coagulopathy, or platelet disorder requiring special precautions)
20. Malignancy (Not excluded: a volunteer with a surgical excision and subsequent observation period that in the investigator's estimation has a reasonable assurance of sustained cure or is unlikely to recur during the study period)
21. Psychiatric condition that compromises safety of the volunteer or precludes compliance with the protocol, specifically excluding persons with psychoses within the past 3 years, ongoing risk for suicide, or history of suicide attempt or gesture within the past 3 years
22. All healthcare workers with direct patient contact
23. Childcare worker who has direct contact with children
24. Individuals employed as food handlers or otherwise engaged in the preparation or delivery of food outside of their place of residence
25. A urine toxicology test positive for opioids, cocaine, or amphetamines.

### **7.3 Household Contact Inclusion Criteria**

Household contacts must be deemed eligible according to the following criteria, before the volunteer is vaccinated:

1. Able to understand and give written consent, and complete an assessment of understanding
2. Healthy (based on medical history and physical examination) men or women aged 18-60.
3. Low risk for HIV infection (see Section 18.2) and willing to maintain low-risk behavior for 4 months following the volunteer's vaccination
4. Willing to undergo HIV testing and receive HIV test results and as well as risk-reduction counseling
5. Willing to forgo blood or tissue donation for 4 months after the volunteer's vaccination; for those who test HIV positive due to trial vaccination (vaccine-induced HIV seropositivity), until the anti-HIV antibody titers become undetectable
6. If a woman of child-bearing potential, committed to use an effective method of contraception when sexually active with men for 4 months following the volunteer's receipt of vaccine, including:
  - a. Condoms (male or female) with or without spermicide

- b. Diaphragm or cervical cap with spermicide
  - c. Intrauterine device
  - d. Hormonal contraception
  - e. Successful vasectomy in the male partner (considered successful if a woman reports that a male partner has [1] documentation of azoospermia by microscopy, or [2] a vasectomy more than 2 years ago with no resultant pregnancy despite sexual activity post-vasectomy)
  - f. Not be of reproductive potential, such as having undergone hysterectomy, bilateral oophorectomy, or tubal ligation
7. All sexually active males (unless anatomically sterile) must be willing to use an effective method of contraception (such as consistent condom use) from the conclusion of the isolation period until at least 4 months after vaccination

#### **7.4 Household Contact Exclusion Criteria**

1. Significant acute or chronic disease, including inflammatory bowel disease or other chronic gastrointestinal disease, immunodeficiency syndrome, or condition requiring immunosuppressant medications (the use of topical or inhaled steroids is permitted)
2. Asthma other than mild to moderate, well-controlled asthma. Exclude a volunteer who:
  - Generally uses a bronchodilator (beta 2 agonist) daily, or
  - In the past year has (any of the following):
    - Had > 1 exacerbation of symptoms treated with oral steroids
    - Routinely used high dose inhaled corticosteroids (e.g., more than the equivalent of 500 mcg fluticasone; 1200 mcg budesonide; 500 mcg beclomethasone; or 1000 mcg triamcinolone/flunisolide, as a daily dose) or theophylline
    - Needed hospitalization, or intubation for asthma
  - Prophylactic bronchodilator use prior to exercise is not exclusionary
3. Pregnant or lactating
4. HIV infection
5. Individuals employed as a healthcare worker with direct patient contact, childcare worker who has direct contact with children <5 years old, or food handler (or an individual who is otherwise engaged in the preparation or delivery of food outside of their place of residence)

## **8 STUDY PRODUCTS**

### **8.1 Study Products**

Detailed instructions for study products including preparation, storage and documentation are provided under separate cover in the Study Operations Manual. Additional information is also provided in the Investigator's Brochure for the rcAd26.MOS1.HIV-Env product.

#### **8.1.1 rcAd26.MOS1.HIV-Env**

rcAd26.MOS1.HIV-Env vaccine is formulated as Acryl-EZE enteric-coated capsules for oral administration. The  $10^8$  and  $10^9$  doses will be administered in size 3 capsules. The  $10^{10}$  and  $10^{11}$  doses will be administered in larger size 1 capsules.

#### **8.1.2 Placebo**

The placebo is formulated as Acryl-EZE enteric-coated capsules for oral administration. Capsules will be size 3.

### **8.2 Handling of Study Treatments**

#### **8.2.1 Packaging and Labeling**

rcAd26.MOS1.HIV-Env and placebo capsules will be provided in Nalgene 1 oz. size plastic amber colored polyethylene container with a polypropylene closure and labeled in accordance with Good Manufacturing Practice (GMP). Ten drug product capsules are packaged per container.

#### **8.2.2 Shipment and Storage**

rcAd26.MOS1.HIV-Env and placebo capsules should be stored frozen at  $-20\text{ }^{\circ}\text{C}$  ( $\pm 10\text{ }^{\circ}\text{C}$ ). One rayon ball is used as packing inside the Nalgene bottles to prevent damage to the capsules during shipping and handling.

#### **8.2.3 Dose preparation and administration**

The unblinded pharmacist (or other unblinded staff member qualified to handle and dispense medication) will dispense rcAd26.MOS1.HIV-Env or placebo capsules in a single dose container labeled with the volunteer's study ID and allocation number. Volunteers will be asked to swallow the capsule(s) with a glass of non-carbonated water.

## **9 CONDUCT OF THE STUDY**

### **9.1 Informed Consent**

The informed consent form documents that a volunteer (1) understands the potential risks, benefits, and alternatives to participation, and (2) is willing to participate in this study. Informed consent encompasses all written or verbal study information staff provide to the volunteer before and during the trial.

The informed consent process continues throughout the study. At each study encounter, staff should consider reviewing the procedures and requirements for that encounter and for the remaining encounters. Additionally, if any new information is learned that might affect the volunteer's decision to stay in the trial, this information will be shared with trial volunteers. If necessary, volunteers will be asked to sign a revised informed consent form.

Volunteers must sign a screening or protocol-specific consent before any procedures to determine eligibility are performed. All recruitment and prescreening materials will be approved by the Institutional Review Board.

#### **9.1.1 Screening Consent Form**

An IRB approved general vaccine screening protocol and consent may be used as part of the initial screening procedure for this trial. Results from this IRB approved general screening or prescreening may be used to determine eligibility in this protocol, provided the tests are conducted within the time period specified in the eligibility criteria.

#### **9.1.2 Protocol-Specific Consent Form**

The protocol-specific consent form describes the study products to be used and all aspects of protocol participation, including screening and enrollment procedures. The consent form is developed in accordance with local IRB requirements and the principles of informed consent as described in Title 45, Code of Federal Regulations (CFR) Part 46 and Title 21 CFR, Part 50, and in the International Conference on Harmonization (ICH) Guideline 4.8.10. It must be approved by all responsible ethical review bodies before any volunteers can be consented for the study.

#### **9.1.3 Assessment of Understanding**

Study staff should ensure that volunteers understand the study before screening them. This process involves reviewing the informed consent form with the volunteer, allowing time for the volunteer to reflect on the procedures and issues presented, and answering all questions completely. An Assessment of Understanding is used to document the volunteer's understanding of key concepts in this HIV vaccine trial. The volunteer must complete the Assessment of Understanding—with the assistance of staff, if necessary, in reading and understanding the questions and responses—before screening. Volunteers must verbalize understanding of all questions answered incorrectly. This process and the volunteer's understanding of the key concepts should be recorded in source documentation at the site.

## **9.2 Clinical and Laboratory Evaluations – Volunteers**

Please see Sections 18.5 and 18.7 for a concise outline of study procedures. Screening should occur within 56 days of enrollment. Volunteers will be admitted to the isolation facility 2 days before the vaccine is administered in order to allow for any incubating illness to emerge prior to the administration of the vaccine. During the isolation period, volunteers will be seen twice daily. For visit windows, refer to the Schedule of Procedures (Section 18.5).

## **9.3 Unscheduled Visits**

Unscheduled Visits/Contacts are visits/contact that are not described in the Schedule of Procedures (Section 18.5). Unscheduled visits may occur any time during the study:

- For administrative reasons, e.g., the volunteer or household contact may have questions for study staff or may need to re-schedule a follow-up visit.
- To obtain laboratory test results from a previous visit.
- For other reasons as requested by the volunteer or site investigator.

All unscheduled visits will be documented in the volunteer's study records on applicable source documents and entered into the Case Report Form (CRF).

## **9.4 Unblinding Visit**

After all volunteers (from all 4 groups) have completed the active follow-up part of the study, and the database is locked, unblinding will occur. Volunteers will be informed as to whether or not they received study product or placebo and whether they have vaccine induced seroreactivity. For those with a false positive HIV serology at the end of the study, follow-up testing will be offered. The unblinding visit may be performed in person or by phone.

## **9.5 Criteria for dose advancement and advancement within a single group**

The SMC will review available safety data including safety data through the 9-day post vaccination safety monitoring period prior to enrollment in the next study group. If any of the pausing criteria in Table 2 (Section 9.8.3) are met, a study pause will be triggered. Otherwise, the next group of volunteers will be enrolled.

## **9.6 HIV Counseling and Testing**

HIV counseling will be performed in compliance with the CDC's guidelines and local guidelines for HIV counseling, testing, and referral. Volunteers and household contacts will be counseled at all scheduled visits during the trial on the avoidance of HIV infection and on the potential negative social impacts of testing antibody positive due to the vaccine. They will also be counseled on the risks of seeking HIV antibody testing outside of the study during study participation and will be discouraged from doing so.

### **9.6.1 Distinguishing intercurrent HIV infection from vaccine-induced seroreactivity**

The study product may elicit an antibody response to HIV proteins. Therefore, vaccine-induced seroreactivity (VISR) may occur in this study. If significant shedding of the

vaccine occurs, it is possible that household volunteers may acquire VISR as well, although considering the attenuated nature of the vector this seems unlikely. Several precautionary measures will be taken to distinguish intercurrent HIV infection from vaccine-induced positive serology.

- Signs or symptoms of an acute HIV infection syndrome, an intercurrent illness consistent with HIV-1 infection, or probable HIV exposure would prompt a diagnostic workup for recent exposure/acute infection testing to determine HIV infection.
- HIV diagnostic testing will be similar to the HIV Vaccine Trials Network (HVTN) HIV testing algorithm, which is able to distinguish vaccine-induced antibody responses from actual HIV infections.
- All volunteers or household contacts who have VISR will be offered post-study HIV-1 diagnostic testing (HIV-1 enzyme immunoassays [EIAs], Western blot, and/or PCR periodically and free of charge as medically/socially indicated (approximately every 6 months).

All volunteers who become HIV-infected during the study will be terminated from the study. Potential and enrolled volunteers identified as HIV-infected will be referred for medical treatment, counseling, and management of the HIV infection. These individuals may also be referred to appropriate ongoing clinical trials or observational studies.

## **9.7 Prior and Concomitant Treatment**

All concomitant medications will be recorded on CRFs from the signing of the ICF until the last study visit. Study volunteers can receive medications such as acetaminophen, non-steroidal anti-inflammatory drugs (NSAIDs), or antihistamines as needed although they must be documented. Use of these medications as routine prophylaxis prior to study vaccination is discouraged.

## **9.8 Study discontinuation**

A volunteer will be taken out of the study in the event of:

- Repeated failure to comply with protocol requirements
- Decision by the study sponsor or PI to stop or cancel the study
- Decision by local regulatory authorities or IRB to stop or cancel the study
- Volunteer's request

### **9.8.1 Early discontinuation or withdrawal of volunteers**

Each volunteer and household contact has the right to withdraw from the study at any time for any reason without affecting the right to treatment by the investigator/designee. Any unnecessary withdrawal from the Isolation Unit before Day 9 (day of discharge) should be strongly avoided. Prior to admission, prior to vaccination, and throughout the isolation period volunteers will be educated as to the importance of remaining on the Isolation Unit through Day 9 (day of discharge). If a volunteer decides to leave the Isolation Unit prematurely, they will be instructed to return daily for shedding samples to be collected through Day 9 post-vaccination.

The investigator should make an attempt to contact volunteers who did not return for scheduled visits or follow-up. Although the volunteer is not obliged to give reason(s) for withdrawing prematurely, the investigator should make a reasonable effort to ascertain the reason(s) while fully respecting the volunteer's rights.

The investigator also has the right to withdraw a volunteer, e.g. because of worsening health status, intercurrent illness, AEs, or pregnancy (for pregnancy follow-up see Section 10.4). The sponsor reserves the right to request the withdrawal of a volunteer due to safety issues, protocol violations, or administrative or other reasons.

Any unnecessary withdrawal should be avoided. Should a volunteer be withdrawn, all efforts should be made to complete and report the observations as thoroughly as possible. Whenever a volunteer is withdrawn from the study, independent of the reason, a final evaluation must be completed for that volunteer and the primary reason for which the volunteer was withdrawn must be stated. All documentation concerning the volunteer must be as complete as possible.

For those volunteers who are unable to continue participation in the study, but who do not withdraw consent, an early termination visit will be conducted. Any volunteer who withdraws consent will not have any further data collected after consent has been withdrawn.

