## Primary Objective

- To evaluate the safety and tolerability of a single oral administration of rcAd26.MOS1.HIV-Env vaccine administered in a dosage escalation of  $10^8$ ,  $10^9$ ,  $10^{10}$ , and  $10^{11}$  viral particles.

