### **10.3.2 Follow-up of ongoing adverse events and assessment of outcome**

#### **10.3.2.1 Follow-up of non-serious adverse events**

Non-serious AEs already documented in the CRF at a previous assessment and designated as 'ongoing' should be reviewed at subsequent visits. If the event has resolved, the documentation in the CRF should be completed. If the frequency or severity of a non-serious AE changes significantly, a new record of the AE has to be started. If the AE becomes serious, the procedures for reporting of SAEs have to be followed (see Section 9.8.3).

New non-serious AEs will be recorded through Month 4 post-vaccination. Ongoing non-serious AEs will be monitored until the Day 365 visit (or until the last study visit for volunteers who withdraw early (see Section 9.8.1)).

Outcomes will be assessed as:

1. Resolved
2. Resolved with sequelae
3. Resolving
4. Not resolved
5. Fatal
6. Unknown

Clinically significant abnormal laboratory values will be followed up until they have returned to normal, stabilized, or a satisfactory explanation has been provided.

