#### **10.4 Handling of pregnancy cases**

Pregnancy events will be reported through 4 months following vaccination. All initial reports of pregnancy must be reported to the IAVI Medical Monitor by the investigational staff within 24 hours of their knowledge of the event using the appropriate pregnancy notification form. Abnormal pregnancy outcomes (e.g. spontaneous abortion, stillbirth, and congenital anomaly) are considered SAEs and must be reported using the Serious Adverse Event Form.

Because the effect of the study vaccine on sperm is unknown, pregnancies in partners of male volunteers included in the study will be reported by the investigational staff within 24 hours of their knowledge of the event using the appropriate pregnancy notification form.

Follow-up information regarding the outcome of the pregnancy and any postnatal sequelae in the infant will be required.

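### After the single Day 0 dose, withdrawal for adverse events, illness or repeated non-compliance stops no treatment but ends scheduled safety follow-up

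*Protocol*

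**What the plan says.** The primary objective (Protocol, Section 1) is "To evaluate the safety and tolerability of a single oral administration of rcAd26.MOS1.HIV-Env vaccine". Dosing is on Day 0 only (Table 1; Section 18.5).

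Three rules take a volunteer out of the study, and none is restricted to the time before dosing:

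- Section 9.8, worded as mandatory: "A volunteer will be taken out of the study in the event of", among other reasons, "Repeated failure to comply with protocol requirements".
- Section 9.8.1, at the investigator's discretion: "The investigator also has the right to withdraw a volunteer, e.g. because of worsening health status, intercurrent illness, AEs, or pregnancy". The sentence goes on to refer to Section 10.4 for pregnancy follow-up.
- Section 9.8.1, at the sponsor's request: "The sponsor reserves the right to request the withdrawal of a volunteer due to safety issues, protocol violations, or administrative or other reasons".

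On what happens next, Section 9.8.1 says: "Whenever a volunteer is withdrawn from the study, independent of the reason, a final evaluation must be completed for that volunteer". It adds an early termination visit for those who cannot continue but have not withdrawn consent. Section 10.3.2.1 has ongoing non-serious AEs monitored to Day 365, "or until the last study visit for volunteers who withdraw early".

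**The concern.** In a multi-dose trial, withdrawal for an adverse event protects the person from further exposure. Here the exposure is complete on Day 0, so withdrawal after dosing ends only observation. The protocol has one concept, leaving the study, and does not separate the end of treatment from the end of follow-up for an individual.

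Safety is the primary outcome, and several of the listed reasons (AEs, worsening health, intercurrent illness, safety issues) are themselves safety outcomes. Loss of follow-up for those reasons is informative: the volunteers whose later course matters most are the ones who may stop being observed. The duration and outcome of the event, any worsening, and new events of other kinds could go unrecorded, and the safety profile would then look milder than it is. The vector is also replication competent, so shedding samples not taken cannot be recovered later.

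**Working it through.** **1. What follow-up survives a withdrawal, and what does not**

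| Item | After withdrawal | Source |
|---|---|---|
| Reported SAEs | Followed until resolved, stable or explained, for at most 12 months; no exemption for withdrawn volunteers | 10.3.2.2 |
| Pregnancy | Outcome and infant follow-up required | 10.4 |
| Clinically significant laboratory abnormalities | Followed until normal, stable or explained | 10.3.2.1 |
| Ongoing non-serious AEs | Only to the last visit | 10.3.2.1 |
| Scheduled collection of new AEs to Day 112 and SAEs to Day 365 | No later visit provided | 9.8.1, 10.1.2, 18.5 |
| Remaining swabs, safety laboratory tests, HIV tests | No later visit provided | 9.8.1, 18.5 |

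For the fourth row, Section 10.3.1 follows vaccine-related AEs to resolution or study completion and makes no exception for early withdrawal. That does not agree with 10.3.2.1.

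**2. Observation time lost**

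Inputs: AE collection to Day 112 and SAE collection to Day 365 (10.1.2.2). For withdrawal at Day d with no later contact, the loss is (112 − d)/112 for AEs and (365 − d)/365 for SAEs.

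| Withdrawal | AE days lost | SAE days lost | Swab visits lost |
|---|---|---|---|
| Day 9 | 103/112 = 92.0% | 356/365 = 97.5% | Days 12, 17, 21, 28 |
| Day 28 | 84/112 = 75.0% | 337/365 = 92.3% | only weekly repeats, if PCR is positive at Day 28 |
| Day 112 | 0 | 253/365 = 69.3% | only weekly repeats, if still running |

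After Day 28, the safety laboratory tests at Days 112 and 365 and the HIV test at Day 365 (18.7) are also lost.

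**3. Which endpoints are touched**

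Section 12.2 sets three safety windows: 9 days for solicited reactions, 4 weeks for related unsolicited AEs, and 4 months for any AE with 12 months for SAEs. A Day 28 withdrawal leaves the first two complete and cuts only the third.

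**4. The plan's precision figures**

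The two-sided 95% Clopper-Pearson upper limit for 0 of n is 1 − 0.025^(1/n). It gives 60.2% for n = 4 and 52.2% for n = 5, as stated in Section 12.3. These figures do not measure the present problem. Section 12.1.1 keeps every dosed volunteer with any post-dose data in the safety population, so the denominator stays at 5. A vaccinee withdrawn for an AE has an event on record, 1 of 5 (95% CI 0.5% to 71.6%).

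**The case against.** The strongest reply is that the protocol keeps more than the withdrawal rule suggests. The first three rows of the first table stand. Withdrawal for an AE is discretionary, and 9.8.1 asks that unnecessary withdrawals be avoided and that observations be completed as fully as possible. Mandatory removal requires repeated non-compliance, not a single lapse. A volunteer who leaves isolation early is asked to return daily for swabs through Day 9. Data after Day 9 do not enter the scheduled dose-escalation review. The share of days lost is calendar time, not a share of lost events. All of this is correct and limits the point. None of it provides later scheduled visits for a withdrawn volunteer.

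Three stronger readings are tempting but are not supported:

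- A reader might infer a conflict between withdrawal for pregnancy and Section 10.4. There is none: 9.8.1 itself points to 10.4, which states: "Follow-up information regarding the outcome of the pregnancy and any postnatal sequelae in the infant will be required".
- A reader might infer that one withdrawal takes a dose group from 5 to 4 and so moves the zero-event limit from 52.2% to 60.2%. Section 12.1.1 keeps the volunteer in the population, and the event that led to withdrawal is counted.
- A reader might infer that the Day 112 and Day 365 collection periods contradict the withdrawal rule. Any withdrawal shortens such a period for the person who leaves; that is a cost, not a contradiction.

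**Conclusion.** The point holds in a limited form. After dosing, Sections 9.8 and 9.8.1 permit, and for repeated non-compliance require, removal that stops no treatment and ends scheduled safety follow-up. What is lost is monitoring of ongoing non-serious AEs, active collection of new AEs and SAEs, and any outstanding swabs, laboratory tests and HIV tests. The loss can be related to the primary outcome. The volunteer remains in the safety population, so later events go unseen while the denominator is unchanged, and each vaccinee is one fifth of a dose group.

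At Day 28 the loss would be 75% of the AE period and 92% of the SAE period for that person. This assumes that no contact follows the final evaluation. It is an illustration: the protocol states no withdrawal rate, so the effect on the trial as a whole cannot be estimated. The change is worth making because it is cheap and because Section 9.8.2 already adopts the same principle when the whole study is discontinued: vaccination stops, and active volunteers are still followed.

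**What to change.** Reword Sections 9.8, 9.8.1 and 10.3.2.1 so that, after dosing, scheduled AE and SAE follow-up ends only with withdrawal of consent or loss to follow-up. For the other reasons now listed:

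- allow individual procedures to be omitted;
- allow AE and SAE contacts by phone;
- still collect outstanding shedding swabs where the volunteer agrees, since a phone call cannot replace a swab.

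Two pairs of passages should be reconciled at the same time:

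- 10.3.2.1 (monitoring to the last visit after early withdrawal) with 10.3.1 (vaccine-related AEs followed to resolution or study completion);
- 9.8 (volunteers taken out if the study is stopped) with 9.8.2 (active volunteers followed through their remaining visits).

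The cost is the rewording and, for each volunteer concerned, a few extra contacts or swab visits. No dose, treatment rule or sample size changes.
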